### **Data Management and Analysis**

---

Four sources of data will be assembled and linked to address the study objective: 1) abstracted medical chart documentation of patient demographics, admission and discharge dates, the community drug list, discharge prescription, and admitting and discharge diagnoses, 2) adverse events information and assessment post-discharge, 3) the RAMQ medical services and prescription claims data, and 4) co-intervention data collected by the study co-ordinator. All data will be managed in an Oracle database, and files for individual patients will be linkable through a study identification number and Quebec medicare number, with nominal information retained in a separate encrypted file.

The integrity of randomization will be assessed by characterizing the age, sex, baseline number of visits, hospitalizations, medications, and co-morbidity (using the Charlson co-morbidity index, a weighted index of conditions that increase the risk of mortality) of patients randomized to discharge reconciliation and usual care. The CONSORT guidelines will be followed to document the eligibility and follow-up of patients and inpatient units (clusters) in the trial. The provincial health administrative data will be used to characterize bias related to patients lost to follow-up after discharge for whom adverse drug events cannot be measured, based on the secondary outcome (re-admission/ER visits) as this can be measured on all patients.

An intention to treat approach will be used to analyze study results. To determine whether discharge reconciliation reduces the risk of adverse drug events post-discharge, we will use logistic regression within a generalized estimating equation framework to account for clustering of patients within unit. The presence of a probable or definite adverse event (yes vs. no) will be the outcome variable, hospital unit will be the defined clustering factor, and an exchangeable correlation matrix will be used to account for clustering of patients within unit. Discharge reconciliation will be fit as a dummy variable, using usual care as the reference group. We will use the same approach to assess the secondary outcome, ER visits and/or hospital re-admission. For both the primary and secondary outcome, we will assess, whether adjustment for co-interventions and baseline differences between patients in the usual care and intervention arm confound the effect of the intervention. In secondary analysis, we will assess whether the effect of the intervention is modified by hospital unit type (medicine vs. surgery vs. psychiatric), and patient characteristics that are associated with a higher risk of adverse events (age, number of medications at discharge) by including respective interaction terms in the logistic model and testing their significance using the Wald chi-square statistic.

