## Study Design

A randomized cluster design will be used to determine if electronically-enabled discharge reconciliation reduces adverse events post discharge. The study population will be patients admitted to medical, surgical, and psychiatric units at the McGill University Health Center. Patients will be stratified by medical, surgical or psychiatric admission, and a cluster randomization approach will be used to allocate the 16 medical, 10 surgical, and 2 psychiatric units to discharge reconciliation and communication versus usual care (Figure 3).

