*Sample size:* We based our sample size requirements on the primary outcome for discharge reconciliation—difference in the rate of adverse drug events—as this binary outcome with correlated patient observations required the maximum sample size (appendix 1). For this outcome, we bracketed expected rates of adverse drug events in the control group based on recent Canadian and American studies to be between 10% and 19%. We specified an absolute reduction of 5% as being the smallest clinically relevant difference that would be worthwhile to detect. A difference of this magnitude would conservatively result in 96,000 fewer adverse drug events in Canada annually, at an overall estimated annual cost-savings of \$240million. Specifying an acceptable Type 1 error of 5%, and Type 2 error of 20%, the estimated sample size for the expected range in possible cluster correlations ( $r=0.02-0.05$ ) varies from 2,852 to 4,423 patient admissions, assuming a baseline rate in the control group of 15%, midway between 10% and 19%. Based on an analysis of re-admission rates in 2008, a cluster correlation no greater than 0.03 is expected, which would mean a sample size of 3,376 is required to detect a 5% reduction in adverse drug events. Based on our prior work, we estimate that 10% of patients will not be reached to complete the post-discharge follow-up interview, therefore we estimate that we will need to recruit 3,714 patients to achieve our sample size requirements. Overall, in 2008, there were 17,480 admissions to the MUHC, of which 12,236 were admitted to eligible medical, surgical and psychiatric units. Based on our pilot study, approximately 42% ( $n=5,139$ ) of patients will be eligible for inclusion (i.e. have public drug insurance,  $\geq 18$  years old, first admission in study period, alive at discharge), and of these 3% will refuse to participate, 45% will not be asked for consent because the staff are too busy, and 52% will consent to participate. By providing staff with support to obtain consent from patients, we expect that we can increase the proportion of eligible patients participating to 60%, or 257 per month. Assuming 10 months per year of active recruitment to account for summer and winter holidays, we estimate that it will take 15 months, or approximately 1.5 years to recruit all patients. With an average length of stay of 8.9 days, we can successfully complete enrollment and follow-up in 18-20 months.

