*Randomization:* The 28 hospital units will be assigned a random number, stratified by type (medicine, surgery, psychiatry), and the default random number generator in SAS will be used to randomly assign units within stratum to electronically enabled discharge reconciliation or usual care. There will be approximately 1,857 patients who are assigned to medication reconciliation at discharge, 1,857 to usual care.

---

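### With two psychiatric units in their own stratum, the planned Wald test of treatment by unit type cannot validly assess psychiatry, and with the usual robust GEE variance it would reject far too often

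*Protocol*

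**What the plan says.** Protocol, Study Design: a stratified cluster randomisation is to "allocate the 16 medical, 10 surgical, and 2 psychiatric units" to the two arms. Protocol, Study Population (Randomization): SAS is used to "randomly assign units within stratum to electronically enabled discharge reconciliation or usual care", and "There will be approximately 1,857 patients who are assigned to medication reconciliation at discharge, 1,857 to usual care".

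Protocol, Data Management and Analysis: the outcome model is "logistic regression within a generalized estimating equation framework to account for clustering of patients within unit", and "an exchangeable correlation matrix will be used to account for clustering of patients within unit". Under secondary analysis, "we will assess whether the effect of the intervention is modified by hospital unit type (medicine vs. surgery vs. psychiatric", alongside age and number of medications, by adding interaction terms and "testing their significance using the Wald chi-square statistic". The section does not say whether the GEE variance is robust or model-based, and it has no rule for a stratum with a single unit in each arm.

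**The concern.** Unit type has three levels, so the interaction has two degrees of freedom, and one of them compares the psychiatric treatment effect with the medical one. If one psychiatric unit is in each arm, that effect is the difference between two units. Their ordinary difference in adverse drug event rates and any effect of the intervention are the same quantity in the data.

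The test may also hide this. A robust variance is built from how units differ within an arm and stratum. With one unit in the cell nothing can differ, so the between-unit error in psychiatry is counted as nil. A chance difference between two units can then be read as evidence that the intervention works differently by unit type, in either direction.

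**Working it through.** **The plan's own figure.** The protocol states no error rate or power for the interaction test, so there is nothing to reproduce on this point.

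**Inputs from the protocol.** 16, 10 and 2 units; control rate 15% (bracketed by 10% and 19%); cluster correlation 0.03 expected (range 0.02 to 0.05); 3,376 evaluable patients; 5% type 1 error.

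**Assumptions.** Arms split 8/8, 5/5 and 1/1. Average unit size is 3,376/28 = 120.6, taken as 120 per unit. Unit outcomes are beta-binomial.

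**Step 1: why the robust variance is zero.** In the arm × unit-type model all covariates are constant within a unit. With exchangeable correlation ρ, a unit of size m with events y contributes (y − mp)/(1 + (m − 1)ρ) to its cell's estimating equation, where p is the fitted rate of the cell. The contributions in a cell must sum to zero. With one unit in the cell, y − mp = 0. The squared contribution, which is all the unit adds to the sandwich, is therefore 0 as well. The robust variance of the psychiatric log odds ratio is 0 + 0 = 0. Full GEE fits gave at most 1.4 × 10⁻¹⁶, which is rounding. In one example fit the model-based variance of the same effect was 1.33. With a patient covariate added, the robust variance had a median of about 10⁻⁵.

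**Step 2: hand check of psychiatry vs medicine.** Let v be the variance of one unit's log odds.
- True variance of the contrast: (v + v) + (v/8 + v/8) = 2.25v.
- What the sandwich targets: 0 + 0.25v.
- Ratio 2.25/0.25 = 9, so the z statistic is inflated by √9 = 3.
- Rejection rate: P(|Z| > 1.96/3) = P(|Z| > 0.653) = 0.51.
- The sandwich also runs low with 8 medical units per arm. Allowing for this: P(|t₁₄| > 1.96/(3 × √(16/14))) = P(|t₁₄| > 0.611) = 0.55.

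**Step 3: simulation with no effect modification** (20,000 trials per scenario, nominal 5%).

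| Test | Rejection rate |
|---|---|
| 2-df, robust uncorrected, correlation 0.03, no effect | 0.64–0.645 |
| Same, common odds ratio (15% to 10%) | 0.66 |
| Same, correlation 0.02 to 0.05 | 0.64–0.66 |
| Psychiatry vs medicine alone, robust, correlation 0.03 | 0.57–0.58 |
| 2-df, model-based, correlation estimated (0.03) | about 0.10 |
| 2-df, model-based, correlation known (0.03) | about 0.03 |
| Medicine vs surgery, robust uncorrected | 0.09–0.10 |
| Medicine vs surgery, corrected, t(22) | about 0.056 |

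In the last row each arm-by-type variance is multiplied by k/(k − 1), that is 8/7 for medicine and 5/4 for surgery. The reference has 26 units − 4 cells = 22 degrees of freedom. A check with 300 full GEE fits gave 0.63 for the 2-df robust test, and 0.64 with a patient covariate.

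**Step 4: sensitivity of the 2-df robust test.** Baseline rate 10%: 0.65; 19%: 0.64. Unit-size coefficient of variation 0.5: 0.655. Psychiatric units of 30, 60 or 200 patients: 0.70, 0.67, 0.64. Correlation close to zero: 0.63. All units at 30 patients: 0.635, so the result does not hinge on the assumed unit size.

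**The case against.** - **The variance estimator is not named.** Data Management and Analysis gives the model, the cluster, the working correlation and the test, and stops there. The choice of covariance estimator and any small-sample correction often sits in a statistical analysis plan, which is not at hand. A reader might infer that the planned test will reject about two times in three whatever is done. The protocol does not support that: the figure holds for the uncorrected robust variance, and with model-based variance the rate is about 3–10%. This objection stands for the size of the error. It does not remove the problem, because model-based variance takes the psychiatric between-unit error wholly from the medical and surgical units, and two psychiatric units in opposite arms cannot check that.
- **One unit per arm is inferred.** The protocol's equal split counts patients, not units. That stands as a caveat, but the alternative is no better: if both psychiatric units fell in one arm, the psychiatric interaction could not be estimated.
- **The variance is not always exactly zero.** That needs a model with only arm, unit type and their product, while the protocol also plans covariate adjustment. The rejection rate barely changes when a covariate is added.
- **The consequence is limited.** This is a secondary analysis. A reader might infer that a false psychiatric finding is very likely, or that it would steer implementation in psychiatric units. The psychiatric contrast alone rejects in 57–58%, and no section plans a psychiatry-specific decision; Expected Contribution & Knowledge Translation ties policy use to whether the intervention reduces adverse drug events overall.

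**Conclusion.** The concern holds in a conditional form. The protocol itself fixes a three-level unit type, two psychiatric units randomised within their own stratum, and a Wald test of the interaction. That combination cannot separate arm from unit in psychiatry, whichever variance is used, given one unit per arm.

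The size of the false-positive rate depends on a choice that the protocol leaves open: about 64–66% at nominal 5% with the usual uncorrected robust variance, and about 3–10% with model-based variance. The high figure is stable over the protocol's ranges for cluster correlation and baseline rate. Confidence is high for the non-separability; the 64–66% rests on the assumed estimator.

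A reader might extend this to the main result. That does not follow: the overall treatment effect is estimated across all 28 units, so no arm rests on a single unit, and the primary test is not affected in this way. This should be corrected, but it does not threaten the trial's primary conclusion.

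**What to change.** In Data Management and Analysis:

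1. Limit the formal unit-type interaction test to medicine vs surgery, using a small-sample-corrected robust variance and a t or F reference. In the check this brings the error rate from about 10% to about 5.6%. The k/(k − 1) correction with 22 degrees of freedom is one workable choice among several.
2. Report the two psychiatric units descriptively, and state that unit and arm cannot be separated there.
3. Keep both psychiatric units in the primary analysis.

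This takes a sentence or two and changes neither recruitment, randomisation nor the primary analysis. The cost is giving up a formal psychiatric subgroup test, which the design cannot support.

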### **Monitoring Study Outcomes: Trial Termination Decision Rules and Other Ethical Considerations**

---

To monitor any unintended adverse effects arising from the study intervention(s), we will establish an independent data monitoring board, chaired by [name] (Harvard University), and including [name] (Harvard University), and [name] (McMaster University), scientists who provide pre-eminent expertise in adverse drug events, computerization of health care, and biostatistics. The data monitoring board will monitor quarterly statistics on hospital re-admission and ER visit rates to assess unintended effects, blinded to study group. The study team will be responsible for providing any additional statistical information that are deemed necessary by the data monitoring board to ensure patient safety.

Patients who may not be able to consent at the time of admission because they are cognitively impaired or unable to communicate will be followed up by the research assistant to determine if the patient is able to provide an informed consent. Patients who are able to consent and choose not to enroll at that point will be excluded from the study.

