## Preventable Adverse Drug Events

Up to a quarter of admissions to acute care hospitals are related to adverse drug events (ADE). ADEs are the 6th leading cause of death at a cost over \$5.6 million per hospital per year. Fortunately, at least 58% of these ADE's are preventable, as they result from incomplete drug information, prescribing or dispensing errors, and overuse or underuse of medications. The convergence of increasingly complex care plans, an aging patient population, and multiple transfers between care settings (long term, acute care, community) account for most of the preventable errors that ultimately result in ADEs. In fact, at admission, 60%-70% of medication histories contain at least one error, the majority of which are errors in omitted medication, and 37% have the potential to cause harm^3-8. Failure to obtain a complete profile of pre-admission medication is responsible for 72% of potential adverse drug events after discharge. An estimated 19% to 23% of patients will have an adverse event within 30 days of discharge, 14.3% will be readmitted, and 70% of these events will be related to prescription medication.

---

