## Study Objective

To determine if an electronically-enabled discharge reconciliation intervention that includes:

- 1) electronic retrieval of community drug lists from community pharmacy records,
- 2) reconciliation of community and hospital drugs at discharge, and
- 3) communication of treatment changes to the community-based prescribing physicians & pharmacists

will reduce the risk of adverse drug events (ADEs), ER visits and re-admissions in the 30 days post-discharge compared to usual care.

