**Bias Control** The main challenge in *bias control* is the inability to blind staff to treatment assignment, and potential co-intervention. To control bias, the research assistant, expert panel, and analyst assessing the outcome of treatment will be blinded to unit and treatment allocation status. To assess bias related to possible co-interventions, the project coordinator will conduct a monthly review with the unit directors and hospital pharmacy to assess co-interventions (new initiatives that may modify the study outcomes), and we will use sensitivity analysis to assess the potential impact on the study outcomes. As the involvement of the hospital pharmacist in the patient's care likely reduces the risk of adverse events (e.g. through medication review), we will retrieve this information from the chart and assess whether hospital pharmacist intervention (yes vs. no) is a confounder by including this information as a patient-level variable in the analysis. In addition, as cluster randomization may not produce patients groups who have an equivalent risk of adverse events post-discharge (i.e. because randomization is by unit rather than by patient), we will assess whether patients admitted to the usual care vs. e-discharge units had a similar rate of hospitalizations, and ER visits in the 12 months prior to admission using RAMQ medical service data retrieved for each patient, and include prior ER/hospitalization history in the analysis to determine if it confounds the estimated effect of the intervention.

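### The monitoring board's routine quarterly rates are blinded to study group, so they cannot show whether an effect on re-admission or ER visits is harm or benefit, and the text does not provide for giving the board arm identity.

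*Protocol*

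**What the plan says.** The protocol section on monitoring study outcomes gives the board's purpose: "To monitor any unintended adverse effects arising from the study intervention(s), we will establish an independent data monitoring board". The board's routine material follows. It is to "monitor quarterly statistics on hospital re-admission and ER visit rates to assess unintended effects, blinded to study group". The section does not say whether the rates are pooled over both groups or shown for two unlabelled groups.

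The next sentence opens a route to more information: "The study team will be responsible for providing any additional statistical information that are deemed necessary by the data monitoring board to ensure patient safety". It mentions neither allocation nor the opening of codes.

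Two other parts of the protocol bear on this. The Study Objective states the hoped-for direction for the same outcomes: the intervention "will reduce the risk of adverse drug events (ADEs), ER visits and re-admissions in the 30 days post-discharge compared to usual care". The Bias Control paragraph, in the section on interventions, says that "the research assistant, expert panel, and analyst assessing the outcome of treatment will be blinded to unit and treatment allocation status".

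**The concern.** An effect that arises from the intervention can be recognised only by comparing the intervention units with the usual-care units. The board is asked to recognise such effects from figures that do not show which group is which.

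That would matter less for an outcome that could move in only one direction. Re-admission and ER visits can move either way. They are the secondary outcome under Data Management and Analysis, and the trial is run in the hope that they fall. A gap between two unlabelled groups is therefore what the board would see if the intervention works and also what it would see if it does harm.

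What is at stake is the usefulness of routine safety monitoring over about 15 active months of recruitment. An unintended effect is conceivable. Community drugs left off the discharge prescription move automatically to the discontinuation list, and discontinuations are faxed to pharmacies and prescribers. The physician must record a reason, which is a safeguard, and the protocol gives no frequency for errors. The example shows only why direction matters.

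**Working it through.** The protocol states no threshold, boundary or operating figure for the board, so there is no figure to reproduce. The check asks what the board would see under harm and under benefit, for each reading of the blinding.

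**Inputs**

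- Background re-admission of 14.3%, from the background section on preventable adverse drug events ("14.3% will be readmitted").
- A 5-point absolute difference. The protocol uses this size for adverse drug events ("We specified an absolute reduction of 5% as being the smallest clinically relevant difference"); applying it to re-admission is an assumption, for illustration only.
- Equal groups, following the 1,857 and 1,857 patients given under Randomization.

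**Formulas**

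- Pooled rate = (usual-care rate + intervention rate) / 2.
- Unlabelled display = the two rates without group names.

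**Results**

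| True situation | Usual care | Intervention | Intervention minus usual care | Pooled display | Unlabelled display |
|---|---|---|---|---|---|
| Harm | 14.3% | 19.3% | +5.0 points | (14.3 + 19.3)/2 = 16.8% | 14.3% and 19.3% |
| Benefit | 19.3% | 14.3% | −5.0 points | (19.3 + 14.3)/2 = 16.8% | 14.3% and 19.3% |
| No effect, higher background | 16.8% | 16.8% | 0 | 16.8% | 16.8% and 16.8% |

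**Reading the table**

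- Pooled: all three situations give 16.8%. Units are randomized in parallel and the monitoring section names no baseline period. An effect present from launch could therefore leave the pooled rate level from quarter to quarter.
- Unlabelled arms: the board can tell that a difference exists, but harm and benefit look the same.
- The result does not depend on the chosen rates. Swapping the two rates between equal groups always leaves both displays unchanged. Only arm identity separates the first two rows.

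**The case against.** The strongest reply is the sentence on additional information. It puts a duty on the study team, lets the board judge what is necessary for patient safety, and does not exclude arm identity. The blinding phrase describes the routine statistics and does not forbid the board from learning the allocation. If the rates come by coded arm, a visible gap would itself prompt the board to ask. A reader might infer that the board is barred from detecting harm, or that harm would run unseen to the end of recruitment. The documents do not support either. The second would need pooled reporting, no request from the board and no release of arm identity, all together.

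A second reply is that masking a board at first is a recognised choice, because it limits prejudgement while a pattern is still forming. That stands. It would be wrong to infer that blinding an independent board serves no purpose.

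A third concerns statistical signal. It is tempting to argue that a pooled display buries a harm that arm-level data would reveal within a quarter. The arithmetic does not bear this out:

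- One quarter has 3 × 257 = 771 patients. The pooled SE is √(0.168 × 0.832 / 771) = 1.35 points.
- With 771/28 = 27.5 patients per unit and the protocol's cluster correlation of 0.03, the design effect is 1 + 26.5 × 0.03 = 1.80, so the SE is 1.35 × √1.80 = 1.8 points. A 2.5-point rise is 2.5/1.8 = 1.4 SE.
- By arm, with about 385 patients each, the SE of the difference is √[(0.143 × 0.857 + 0.193 × 0.807)/385] = 2.7 points, or 3.6 with the same design effect. A 5-point gap is 5/3.6 = 1.4 SE.

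The ratios are equal. Arm-level data add a concurrent control and a direction, not power in a single quarter.

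Finally, unblinding triggers and boundaries often sit in a board charter or SAP, which is not shown. The section heading names "Trial Termination Decision Rules and Other Ethical Considerations" and the text beneath gives none, but that absence is not counted here. What remains is a rule the protocol does state, namely that the routine rates are blinded.

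**Conclusion.** The point holds as a limited improvement to patient-safety monitoring. As written, the routine quarterly rates cannot show the direction of an effect under either reading, and if pooled they give no concurrent comparison. This follows from the wording and from the rates being an efficacy outcome expected to fall. The 14.3% and the assumed 5 points only illustrate it.

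The request route reduces the problem but does not settle it. The text does not say that arm identity can be supplied. The route runs through the study team, whose outcome analyst is to stay blinded, and under pooled reporting the board would have little to prompt a request. No claim is made about how often harm would be missed or for how long, because the documents give no basis for one.

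**What to change.** Reword the sentence in the monitoring section so that the board receives the quarterly re-admission and ER visit rates by arm. Either identified arms, or coded arms with the key held by the board and opened at its discretion, would do. State in the same place that interviewers, adjudicators and the outcome analyst remain blinded.

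The cost is a change of wording. There are two small downsides. The board may see an emerging trend by arm, which coded arms would soften. Allocation must also be merged into the report without passing through the outcome analyst. Allocation is by hospital unit and cannot be hidden from those who train and support the intervention units, so this is a matter of who does the merge and does not call for extra staff.
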